**Methods and analysis:**

COINCIDE will: (i) assess phenotypic and genotypic colistin resistance in *E. coli* from humans and poultry; (ii) estimate transmission of colistin resistant *E. coli* between humans and animals; (iii) explore colistin and antimicrobial use (AMU) at the community level; (iv) identify social and cultural factors driving AMU; and (v) strengthen multisectoral One Health collaboration. Post-ban sampling will be conducted in three districts of Central Java Province (Klaten, Karanganyar, and Sukoharjo), where pre-ban samples were already available. We will recruit participants from primary healthcare centers (PHC) (*n* = 683), poultry farmers (*n* = 120), and visit a total of 60 small-scale layer farms. Broiler isolates (*n* = 2865) from Indonesia's routine antimicrobial resistance (AMR) surveillance (2018–2023) will also be included. In terms of sample collection, post-ban samples will include rectal swabs from patients visiting PHC and farmers and boot swabs from small-scale layer farms. Colistin resistance will be screened using CHROMagar COL-APSE agar medium and confirmed by broth microdilution. Results of long-read whole-genome sequencing will identify resistance mechanisms and transmission pathways. A qualitative ethnography work will include participant observation and informal conversations during field visits, alongside in-depth interviews with healthcare professionals and stakeholders. “Drug bag” method interviews will assess antimicrobial use, access, and drivers at the community level. Simulated patient visits to pharmacies and local shops (*warung* or *toko obat*), and interviews with agrovet outlets and poultry shops will be conducted to evaluate compliance with antimicrobial sales regulations.

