### Sample size and sampling strategies

3.2

To detect a meaningful reduction in colistin resistance from an estimated 15% before the ban to 10% afterward, power calculations indicated the need to analyze at least 683 *E. coli* isolates and risk factor surveys from both human and poultry sources. The retrospective (pre-ban) isolates include 577 archived human isolates from primary health care centers (PHC), 2182 broiler surveillance isolates, 513 layer chicken isolates, and 63 layer farmer isolates from 2014. Regarding the prospective sampling, human participants (*n* = 683) will be recruited from PHC, with eligibility criteria including adults over 18 years without current diarrhea or vomiting, who provide informed consent for rectal swab collection. Random selection via raffles of clinic attendees meeting these criteria will be used to minimize selection bias.

Up to 60 small-scale laying hen farms will be sampled to get an estimated 683 bacterial isolates, identified through local livestock office records. The small-scale layer farm is defined as having fewer than 10,000 layer chickens. Boot swabs will be collected from poultry houses. Farm workers (two or three from each farm, *n* = 120) will also be invited to provide rectal swab samples, enabling paired human-animal analysis. We will document recruitment and refusal rates in each setting to assess potential selection bias. All field teams will follow standard operating procedures developed by the COINCIDE consortium for sample labeling, cold-chain maintenance, and data recording to ensure quality and traceability. Additionally, available AMR data from the national broiler surveillance program from 2018 to 2023 will be incorporated. Within this surveillance program, approximately 800 caecal samples are collected from broilers per year via regional Disease Investigation Centers. From these samples, *E. coli* is isolated, and these isolates are tested for antimicrobial susceptibility including colistin using broth microdilution. These data provides a national perspective on resistance trends before and after the ban.

The complete COINCIDE sample scheme is also illustrated in Fig. 3.

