### Data management plan and data analysis

3.6

All data will be securely stored using the Yoda database and ODK data collection forms [40]. Personal identifiers will be pseudonymized or removed to preserve confidentiality. These data will only be available exclusively to principal investigators and data collectors. We will conduct periodic data audits and cleaning to ensure completeness and accuracy. Qualitative data will be analyzed using NVivo version 14. Genomics data will be analyzed using the command line and public bioinformatics resources, where available. All statistical analyses will be carried out using appropriate software such as R version 4.2.3, with a significance level of 0.05, adjusted for multiple testing, applied throughout unless otherwise specified.

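### The 683 in section 3.2 is the size for independent observations with no design effect, although human participants are drawn within health centres; the resulting power loss depends on a centre count and ICC that the protocol does not give

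*Protocol article*

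**What the plan says.** Section 3.2 (Sample size and sampling strategies) sets the target effect as a fall "from an estimated 15% before the ban to 10% afterward" and reports that "power calculations indicated the need to analyze at least 683" isolates, with risk factor surveys, from human and poultry sources. Power and sidedness are not stated. Section 3.6 gives the significance level, "with a significance level of 0.05, adjusted for multiple testing, applied throughout unless otherwise specified".

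The post-ban human sample is then set at the same number, 683. These participants "will be recruited from PHC, with eligibility criteria including adults over 18 years", and within the clinics "Random selection via raffles of clinic attendees meeting these criteria will be used to minimize selection bias". The comparison group is an archive of 577 human isolates, also from PHCs, dated 2014. Section 3.1 places the work in three districts of Central Java. Section 3.4 takes one colony per human sample, so each participant contributes one observation.

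The text gives no number of PHCs, no number of participants per PHC, no ICC and no design effect. It does not say whether the PHCs that supplied the 2014 isolates will be used again. Section 3.2 refers to Fig. 3 for the full sample scheme, and that figure is not available here.

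**The concern.** A raffle among attendees deals with who is picked inside a clinic. It does not make attendees of different clinics exchangeable. Section 3.3.1 lists diet, recent antimicrobial use, animal contact, and water and sanitation as candidate risk factors for resistant carriage. Some of these are plausibly more alike among people who use the same PHC than among people from different PHCs. Where that is so, 683 participants carry less information than 683 independent ones. The design effect is 1 + (m − 1) × ICC, where m is the number per PHC, so a low ICC can still matter when m is large.

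At stake is what the human comparison can show. If the true power is materially below what 683 implies, a non-significant change in human carriage could be read as evidence that the ban had no effect in people, when the study was not able to see a five-point fall reliably.

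**Working it through.** **Inputs from the protocol.** p1 = 0.15, p2 = 0.10 and target 683 (section 3.2); alpha 0.05 (section 3.6); 577 pre-ban and 683 post-ban human isolates (section 3.2); one isolate per person (section 3.4).

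**Assumed, because the documents do not give them.** Two-sided test and 80% power (inferred from the match in step 1); number of PHCs k = 9, 15, 30 or 60; equal PHC sizes; ICC 0.001 to 0.02; different PHCs in the two periods.

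**Step 1: reproduce 683.** Two proportions, unpooled variance:

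n = (0.15 × 0.85 + 0.10 × 0.90) × (1.960 + 0.842)² / 0.05² = 682.85 per group, rounded up to 683.

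The pooled-variance version gives 686. Others do not fit: 540 for one-sided 80% power, 726 with a continuity correction, 914 to 918 for 90% power. The exact match leaves no room for a design effect.

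**Step 2: use the real pre-ban number.** With 577 v 683, independent observations:

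SE = √(0.1275/577 + 0.0900/683) = 0.01878; 0.05/0.01878 = 2.662; power = Φ(2.662 − 1.960) = 75.9%.

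With the pooled variance it is 76.6%. About 4 points of the shortfall from 80% therefore come from the archive and not from clustering.

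**Step 3: add clustering.** In each period, effective n = n / [1 + (n/k − 1) × ICC], put into the formula of step 2. Example with 15 PHCs and ICC 0.01:

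- Pre-ban: m = 577/15 = 38.5, design effect 1.375, effective n = 419.7.
- Post-ban: m = 683/15 = 45.5, design effect 1.445, effective n = 472.6.
- SE = √(0.1275/419.7 + 0.0900/472.6) = 0.02223; 0.05/0.02223 = 2.249; power = Φ(0.289) = 61%.

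Power over the grid:

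| ICC | 9 PHCs | 15 PHCs | 30 PHCs | 60 PHCs |
|---|---|---|---|---|
| 0 | 76% | 76% | 76% | 76% |
| 0.001 | 73% | 74% | 75% | 75% |
| 0.005 | 63% | 68% | 72% | 74% |
| 0.01 | 54% | 61% | 68% | 72% |
| 0.02 | 41% | 51% | 62% | 69% |

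**Step 4: the favourable case, same PHCs in both periods with PHC modelled.** The stable part of the PHC effect cancels. The variance of the difference becomes 0.1275 × DE₁/577 + 0.0900 × DE₂/683 − 2ρ × ICC × √(0.1275 × 0.0900)/k, where DE₁ and DE₂ are the design effects of step 3 and ρ is the correlation of a PHC's effect between the periods. At ICC 0.01 and an assumed ρ of 0.8, power is 70% / 73% / 74% for 9 / 15 / 30 PHCs. At ρ = 1 it returns to about 76%.

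**Step 5: the same result as a detectable difference.** Solve 0.15 − p2 = 2.802 × √(0.1275/n₁ + p2(1 − p2)/n₂) for 80% power. With 577 and 683 independent observations, p2 = 9.8%. With 419.7 and 472.6 (15 PHCs, ICC 0.01), p2 = 8.9%.

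**The case against.** The strongest reply is that the size of the harm rests on two numbers that are not in the documents. That is correct. At ICC 0.001 power stays at 73–75%, and with 60 PHCs at ICC 0.01 it is 72%. Both are close to the independent-data 76%. A reader might infer that even a small between-centre correlation must take the human comparison well below its implied power. The documents do not support that: whether the loss is trivial or large depends on the PHC count, the ICC and whether the 2014 PHCs are used again.

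Second, the shortfall from 80% should not all be charged to clustering, since the archive of 577 accounts for about 4 points. The 80% is itself inferred. This stands and is separated out in step 2.

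Third, a reader might infer that the study will report a spurious fall because its test ignores PHC. Under a naive test with different PHCs in the two periods, the true error rate at a nominal 5% would be about 10–13% for 15 to 9 PHCs at ICC 0.01. But the protocol specifies no before–after test: section 3.6 gives only software, alpha and multiplicity. The model may well be set out in an analysis plan that is not shown, so its absence from the article is no fault.

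Fourth, the article does not say how PHCs are chosen. If every PHC in a defined set is used, and the same set supplied the 2014 isolates, PHC acts more like a stratum than a sampled cluster. This is possible, but nothing in the text establishes it. For the same reason, one cannot say that 683 should be spread over more PHCs than planned.

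What the objections do not remove is the sample-size statement. It is printed in the article, it equals the unadjusted figure, and a suitable clustered model in an unseen plan would not by itself restore the power that 683 implies.

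**Conclusion.** The point holds in a limited form. It is established from the document that 683 is the per-group size for independent observations, with nothing added for recruitment within PHCs. It also follows that the available 577 v 683 gives about 76% power, and not the implied 80%, before any clustering is considered.

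The further loss is conditional. With equal PHC sizes and different PHCs in the two periods, power runs from 75% (30 or 60 PHCs, ICC 0.001) down to 41% (9 PHCs, ICC 0.02). If the same PHCs were sampled in 2014 and PHC is modelled, the loss is smaller and may vanish. Section 3.6 also says that the 0.05 level is adjusted for multiple testing, which would lower power further by an amount that cannot be computed from the text. This should be corrected, but it does not invalidate the design.

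**What to change.** In section 3.2, state the power and sidedness behind 683. Then restate the power or detectable difference for 577 v 683, using the actual number of PHCs in each period and a stated range of ICC values. Say whether the 2014 PHCs are being used again.

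For the human before–after comparison, treat PHC as the cluster, through a random intercept or cluster-robust errors with a small-sample correction. Include district as a fixed term, and compare within PHC where the centres overlap between periods. If an existing analysis plan already specifies this, only the sample-size statement needs to change.

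The cost is a less favourable stated power and wider intervals than an unclustered analysis would give. No extra participants are needed.

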### Laboratory protocols

3.4

Laboratory protocols will be developed iteratively in collaboration with local laboratories, given options for capacity building and limited resources available. Human rectal swab and poultry/environmental boot swab samples will be cultured for *E. coli* on MacConkey agar. For human isolates, bacterial identification will be done using an automatic machine (VITEK® 2 COMPACT, bioMerieux). One presumptive *E. coli* colony per human sample and 15 *E. coli* isolates from boot swabs from layer farms will be selected. For animal isolates, *E. coli* isolates will be confirmed using biochemical tests. In parallel, isolates will be plated on CHROMagar™ COL-APSE (selective medium) in a tailor-made spot-test protocol that allows screening up to eight isolates per plate to screen for colistin-resistant growth. The protocol has been published on https://www.protocols.io, and the video protocol is available online (https://youtu.be/KC1x9u4d02g). Each batch of CHROMagar plates will include a colistin-susceptible *E. coli* strain (ATCC 25922) and a known *mcr*-1-positive *E. coli* as negative and positive controls, respectively. All isolates that grow on CHROMagar (presumptive colistin-resistant) will be tested using automated broth microdilution system (Sensititre, ThermoFisher) to determine colistin MIC, following the most recent EUCAST/CLSI standards. MIC results will be interpreted using the EUCAST MIC and ECOFF database. The ECOFF for colistin resistance in *E. coli* is ≤2 mg/L [42]. All isolates will be catalogued and stored at −80 °C in laboratories in Indonesia. Colistin-resistant *E. coli* isolates will be sequenced using Oxford Nanopore Technologies (ONT) long-read sequencing. DNA extraction, library preparation, and sequencing will be performed in-country by trained local staff. Where relevant, the Microbiology Investigation Criteria for Reporting Objectively (MICRO) framework will be followed in reporting [43].

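### The layer sample of 683 isolates is sized for independent observations but comes from at most 60 farms, so the layer before-after comparison falls short of 80% power

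*Protocol article*

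**What the plan says.** Section 3.2 sets the target: "To detect a meaningful reduction in colistin resistance from an estimated 15% before the ban to 10% afterward". It gives no power, sidedness, ICC or design effect, only the outcome of the calculation: "power calculations indicated the need to analyze at least 683" (the unit being *E. coli* isolates). Section 3.6 gives the significance level: "with a significance level of 0.05, adjusted for multiple testing, applied throughout unless otherwise specified".

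The same 683 then serves two different sampling structures:

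- **Humans.** 683 participants are recruited from PHCs, and section 3.4 takes one colony from each human sample.
- **Layers.** "Up to 60 small-scale laying hen farms will be sampled to get an estimated 683 bacterial isolates". Section 3.4 adds that 15 *E. coli* "isolates from boot swabs from layer farms will be selected", without saying whether 15 is per farm, per swab or per house. The Abstract gives the farm count as a total of 60, not as a ceiling.

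The pre-ban layer comparator in section 3.2 is "513 layer chicken isolates" from 2014. The number of farms that supplied them is not given.

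**The concern.** In the PHC arm 683 isolates means 683 people. In the layer arm it means at most 60 farms, with about 11 isolates each on average. Isolates from one farm come from the same birds under the same antimicrobial practice, and section 3.3.1 collects flock management, biosecurity and antimicrobial use from the farmer, that is, by farm. If resistance varies between farms at all, those isolates carry less information than the same number of unrelated ones.

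At stake is the layer before-after result, one of the study's readings of a national policy. If it is underpowered, a real 5-point fall can easily be missed and read as a ban that did not work. If the isolates were tested as though independent, the intervals would be too narrow and a chance difference could pass for an effect.

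**Working it through.** **Inputs from the article.** Resistance 15% before and 10% after; 683 isolates; at most 60 farms; 15 isolates from layer boot swabs; 513 pre-ban layer isolates; significance level 0.05.

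**Inputs assumed.** Two-sided test and 80% power (chosen because they reproduce 683); ICC from 0 to 0.3; 60 farms actually reached; the pre-ban design effect either equal to the post-ban one or equal to 1.

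**Step 1: reproduce 683.**

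n per group = (1.960 + 0.842)² × (0.15×0.85 + 0.10×0.90) / 0.05², which with unrounded normal quantiles is 682.85, rounded up to 683.

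The pooled-variance formula gives 686 and the arcsine formula 681. Two-sided 90% power gives 915 to 918. The match with the simple formula is exact, which leaves no room for a design effect.

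**Step 2: power with no clustering.** Against 513 pre-ban isolates:

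SE = √(0.1275/513 + 0.09/683) = 0.0195; power = Φ(0.05/0.0195 − 1.960) ≈ 73%.

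So the step from 80% to 73% is due to the smaller pre-ban group, not to clustering.

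**Step 3: add clustering.** Mean isolates per farm m = 683/60 = 11.38; design effect DEFF = 1 + (m − 1) × ICC; effective n = n/DEFF.

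Example at ICC 0.1: DEFF = 1 + 10.38 × 0.1 = 2.04; post-ban effective n = 683/2.04 ≈ 335; pre-ban, if equally clustered, 513/2.04 ≈ 252. SE = √(0.1275/252 + 0.09/335) ≈ 0.0278; power = Φ(0.05/0.0278 − 1.960) ≈ 43%.

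| ICC (assumed) | DEFF | Effective post-ban n | Power, both periods equally clustered | Power, only post-ban clustered |
|---|---|---|---|---|
| 0 | 1.00 | 683 | 73% | 73% |
| 0.05 | 1.52 | 450 | 55% | 66% |
| 0.1 | 2.04 | 335 | 43% | 59% |
| 0.3 | 4.12 | 166 | 24% | 43% |

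A pooled-variance test gives 74%, 56%, 45% and 26% with both periods clustered, and 74%, 64%, 56% and 36% with only the post-ban side clustered. The conclusion is the same.

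**Step 4: does the larger reading of the layout rescue it?** If 15 is per farm, 60 × 15 = 900 isolates, against an estimated 683; conversely 683/15 ≈ 46 farms. With 900 isolates:

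- At ICC 0, power against 513 is 76% (79% with the pooled-variance test).
- At ICC 0.1, DEFF = 1 + 14 × 0.1 = 2.40, effective n = 375, and power is about 41% if both periods are equally clustered.
- The effective n stays at 683 or more only if ICC ≤ (900/683 − 1)/14 ≈ 0.023.

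With 46 farms at 15 each (about 683 isolates), ICC 0.1 gives an effective n of about 285.

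**Step 5: error rate, conditional on an unadjusted analysis.** If isolates in both periods were equally clustered but tested as independent, the true two-sided error of a nominal 5% test would be 2 × (1 − Φ(1.960/√DEFF)): about 11%, 17% and 33% at ICC 0.05, 0.1 and 0.3.

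**The case against.** The best reply has five parts.

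- **The ICC is unknown, and so is the number of 2014 farms.** True, and the size of the loss is therefore a range. The shortfall itself does not depend on either: two-sided power is below 80% at ICC 0 and only falls from there. A one-sided 5% test would start at 83% for 683 against 513, but it is already just under 80% at ICC 0.01, and a one-sided test at 80% power does not reproduce 683.
- **An unseen analysis plan may use a cluster-adjusted model.** It may, and nothing in the article says isolates will be tested as independent. The inflated error rates are therefore conditional and not a charge against the plan. But such a model corrects the standard errors without restoring power, and the sample size is stated here.
- **The farm and isolate counts need not conflict.** Section 3.4 does not say that 15 is per farm. Even if it is, 60 can be a ceiling and 683 an expected yield after confirmation (683/900 is 76%). This stands: the numbers are unclear rather than demonstrably contradictory, and need one clear statement.
- **The observed fall may be larger than 5 points.** Table 1 lists 18.1% to 5.0% for chickens in China by MIC. For a fall of that size, power would be about 93% even at ICC 0.3 in both periods. So the arm is not useless, but that is another country and not the target the article chose.
- **The design as a whole still works.** A reader might infer that the study cannot deliver its 15% to 10% comparison at all. The documents do not support that. The PHC arm takes one colony per person, the broiler surveillance series is not drawn from these farms, and the layer contrast is not named as primary.

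A reader might also take "isolates and risk factor surveys from both human and poultry sources" to promise 683 poultry surveys. The sentence can equally be read as pooling sources, and section 3.3.1 has farmers reporting at farm level, so no such claim is established.

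**Conclusion.** The point holds for the layer arm. The 683 is an independent-observations sample size applied to isolates from at most 60 farms, and the stated layer sample does not reach 80% power for the article's own 15% to 10% target. About 7 points of the shortfall come from having only 513 pre-ban isolates. The rest comes from clustering: power of 55% to 24% for ICC 0.05 to 0.3 with both periods equally clustered, or 66% to 43% with only the post-ban side clustered.

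These figures rest on an assumed ICC range, an inferred two-sided 0.05 and 80% power, an average of 11.4 isolates per farm with all 60 farms reached, and no multiplicity adjustment. Fewer farms for the same 683 isolates, or the adjustment that section 3.6 announces, would lower power further. The defect is in the stated sample-size justification and should be corrected before the layer result is interpreted.

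**What to change.** 1. In section 3.2, state the power and sidedness behind 683, and give layer power separately, against the 513 pre-ban isolates and with a design effect. Estimate the ICC from the archived layer isolates if farm identifiers survive; otherwise show a range of assumed values.
2. State the intended number of farms and the isolates per farm, and say whether 683 is a target or an expected yield, so that the Abstract, section 3.2 and section 3.4 agree. If 15 is per farm, say how 60 × 15 = 900 relates to 683.
3. Specify that the layer comparison is analysed with farm as the cluster (GEE or a mixed logistic model), in both periods where farm identifiers exist.

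No particular number of isolates per farm is recommended. Within 60 farms, changing it moves power little: at ICC 0.1 with both periods equally clustered, power is about 43% for 683 isolates and 41% for 900.

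The cost is wording, a less favourable stated power and somewhat wider intervals. No extra sampling or laboratory work is needed to make these statements.

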#### Quantitative data

3.3.1

Human participants will complete questionnaires that document potential risk factors associated with the carriage of resistant bacteria, including demographics, dietary patterns, recent AMU, animal contact, access to water and sanitation, and medical history. Farmers will provide information on flock management, biosecurity measures, AMU in farm, vaccination, and disease history. Data collection tools, ODK digital surveys [40], will be developed in the local language (Javanese and Bahasa Indonesia) and will be collected by the local Indonesian research team and pre-tested with local research assistants for clarity and cultural appropriateness. Human rectal swabs and poultry boot samples will be transported under a cold chain to the laboratory for processing within 24 h.

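### For the layer farms, refusal rates show how many declined but not whether decliners differ, and any ban-related reluctance would bias the before-after comparison towards a fall

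*Protocol article*

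**What the plan says.** Section 3.2 (Sample size and sampling strategies) names one way of judging selection bias: "We will document recruitment and refusal rates in each setting to assess potential selection bias". The raffle in the same section applies to clinic attendees. For farms, the stated plan is "Up to 60 small-scale laying hen farms will be sampled to get an estimated 683 bacterial isolates, identified through local livestock office records", and two or three workers per farm are invited to give swabs. The pre-ban comparators listed there are "513 layer chicken isolates, and 63 layer farmer isolates from 2014".

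Section 3.3.1 (Quantitative data) adds what participating farms are asked: "Farmers will provide information on flock management, biosecurity measures, AMU in farm, vaccination, and disease history". Section 3.1 fixes 2014 as the date of the archived data, and the Introduction dates the ban to 1 July 2020. The planned effect is given in section 3.2: "To detect a meaningful reduction in colistin resistance from an estimated 15% before the ban to 10% afterward".

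**The concern.** The method and its stated purpose do not match. One refusal rate is compatible with no bias and with a large bias, because the bias depends on who refuses.

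The gap matters more here than in an ordinary survey because the two periods are not alike. In 2014 colistin use was not prohibited. After the ban, farms found through an official register are asked about antimicrobial use. If farms still using colistin are more reluctant to take part, and carry more resistance, the post-ban sample loses resistant isolates for a reason that had no counterpart in 2014. The error runs towards concluding that the ban works.

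Information on decliners has to be taken when the farm is approached. A later analysis plan cannot recover it.

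**Working it through.** **1. The planned effect.** Inputs from the article: 15% and 10% (section 3.2), level 0.05 (section 3.6). Power and sidedness are not stated; 80% and two-sided are assumed. With unpooled variance:

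n = (0.15×0.85 + 0.10×0.90) × (1.95996 + 0.84162)² / 0.05² = 0.2175 × 7.849 / 0.0025 = 682.85, so 683 per group.

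This matches the article ("power calculations indicated the need to analyze at least 683"). The fall at stake is therefore five percentage points.

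**2. Model for selective refusal.** Let s be the share of farms using colistin, pu and pn the prevalence on using and non-using farms, and ru and rn their refusal rates. Assume equal numbers of isolates per farm. Then

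observed = [s(1−ru)pu + (1−s)(1−rn)pn] / [s(1−ru) + (1−s)(1−rn)].

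The article gives none of these five quantities. All values below are assumptions, chosen so that the true post-ban prevalence stays at 15%.

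**3. Illustration.** s = 50%, pu = 25%, pn = 5%, so true prevalence = 0.5×0.25 + 0.5×0.05 = 15%. Only using farms refuse.

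- ru = 50% (overall refusal 25%): using farms are 0.25/0.75 = 33.3% of participants; observed = 0.333×25% + 0.667×5% = 11.7%.
- ru = two-thirds (overall refusal 33%): using farms are 0.1667/0.6667 = 25% of participants; observed = 0.25×25% + 0.75×5% = 10.0%.

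**4. One refusal rate, several answers.** s = 40%, pu = 30%, pn = 5% (true 15%), with overall refusal held at 32.5%:

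| Refusal, using farms | Refusal, other farms | Observed prevalence | Probability of a significant fall |
|---|---|---|---|
| 32.5% | 32.5% | 15.0% | 0.025 |
| 40% | 27.5% | 13.9% | 0.08 |
| 50% | 20.8% | 12.4% | 0.26 |
| 66% | 10% | 10.0% | 0.74 |

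The last column compares 513 with 683 isolates, two-sided 0.05, treating isolates as independent. Correlation within farms and the planned adjustment ("with a significance level of 0.05, adjusted for multiple testing") would lower the larger values. The recorded refusal rate is the same in every row.

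**5. Where the full fall cannot arise.** If pn is above 10%, no amount of refusal by using farms brings the observed figure down to 10%. An example is s = 30%, pu = 25%, where pn = 10.7%. At pn exactly 10%, every using farm would have to refuse. Over a grid of s from 20% to 50% and pu from 20% to 50%, with other farms refusing at 5% to 20%, the remaining feasible cases need about 45% to 87% refusal among using farms.

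**6. Tipping value.** If r is the refusal rate among approached farms and 10% is observed, the fall from 15% vanishes when refusing farms have prevalence

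(0.15 − 0.10(1−r)) / r.

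| r | Tipping prevalence |
|---|---|
| 10% | 60% |
| 20% | 35% |
| 30% | 26.7% |
| 40% | 22.5% |

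The value reaches 100% at r = 0.05/0.90 = 5.6%. Below that refusal rate, refusal could not account for a fall from 15% to 10%, whoever refused.

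**The case against.** Several points on the other side have force.

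- **The article is condensed.** It does not say that nothing else will be recorded, and operating procedures that are not shown may cover refusals. This lowers the certainty of the point. Still, the article names a method and a purpose, and that method does not achieve that purpose.
- **The refusal rate is not useless.** The tipping value needs only the rate and the two prevalences, and a very low rate would settle the matter. This stands, and the fix builds on it.
- **Sub-district and flock size do not reveal colistin use, and a farm hiding prohibited use may not give that as its reason.** This also stands. The log is supporting evidence, and the tipping line carries the weight.
- **The motive is conjecture.** The article nowhere says that using farms would refuse. Its Introduction suggests weak enforcement in the region, which would soften fear of sanctions. Sections 3.6 and 3.7 reduce mistrust through pseudonymised or removed identifiers, restricted access and verbal consent. How farms were recruited in 2014, and who refused then, is not shown.

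A reader might infer more than the article supports. One such reading is that the whole planned fall would probably appear with nothing to warn of it. The full five points need strong differential refusal under invented inputs, and overall refusal of 25% to 33% would itself be on record as a warning. Another is that every result is exposed. Clinic attendees are drawn by raffle and have no ban-related motive. The broiler series is separate national surveillance. Compliance with sales rules is assessed by simulated visits, for which sellers are not asked for consent, and by agrovet-shop interviews, neither of which depends on layer farms agreeing to take part.

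**Conclusion.** The point holds for the layer-farm comparison, the farm-worker comparison and farmer-reported antimicrobial use, and for nothing else. Refusal rates by themselves cannot show whether refusal was selective, and selective refusal tied to the ban would favour a fall. With the inputs of step 3, an unchanged 15% would be seen as 11.7% or 10.0%, depending on whether half or two-thirds of using farms refuse. These sizes rest on assumed use shares, prevalences and refusal rates, on equal isolates per farm, and on no comparable selection in 2014. They show what the stated check cannot exclude and are not a forecast. The change is worth making because it is cheap and the direction of error bears on the study's central question.

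**What to change.** In section 3.2, extend the sentence on refusal for the layer farms:

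- For each approached layer farm that declines, record the reason given and the fields already held in the source of the sampling list ("identified through local livestock office records"), such as sub-district and flock size. Compare these with participating farms, and state that they may not capture colistin use.
- Report beside the layer result a tipping-point line from the observed refusal rate: the prevalence among refusing farms at which the before-after fall would vanish.
- If that prevalence is plausible, word the conclusion as applying to consenting registered farms.

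No refuser log is needed for clinic attendees on this account. If farm recruitment has already begun, the log can cover only the remaining approaches, but the tipping line can still be computed from the documented rates.

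Cost: a few minutes per refusal, one extra table, and possibly a narrower conclusion.
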